### Sample Size

There is no standard procedure for determining the sample size for pilot studies as their main purpose is to obtain an estimate of the standard deviation that could be used to determine the likely effect size to inform a full trial (25). Thus, the proposed study will recruit a total of 44 participants in two groups of 18 allowing for an attrition rate of 20%. This is in line with sample size recommendations for pilot studies (26) and that used in a previous related pilot study of a workplace intervention to reduce sitting (27).

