### Randomization

To minimize contamination between groups in open plan offices, a cluster randomization approach will be used with offices being the unit of randomization i.e., randomization into either the intervention or control group will be assigned on an office basis (28). The number of clusters is projected to be approximately eight with an average cluster size of six (29). Randomization will be achieved by assigning a cluster ID to each office and clusters then being allocated to intervention or control group using an online randomization tool (https://www.randomlists.com/team-generator) by an independent researcher (30). Randomization will take place before the collection of baseline measurements and group allocation will not be disclosed to participants until the completion of baseline assessment (28).

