### Statistical Analysis

All statistical analyses will be performed using SPSS (IBM Corp, Armonk, New York, USA). Data will be assessed for normality using the Shapiro-Wilk test owing to the relatively small sample size. Linear mixed models will be used with arm and time as fixed effects, participant ID and cluster ID as random effects, and the baseline value of each variable as a covariate. An additional linear mixed model will be used to compare the effect of standing vs. sitting posture for the EMA variables at follow-up with posture and arm as fixed effects, participant ID and cluster ID as random effects, and the baseline value of each variable as a covariate. The Sidak *post-hoc* adjustment will be used to adjust for multiple comparisons in all models. Adjustments for missing data will be made using the estimated marginal means procedure of the linear mixed models. If there was a large number of non-normally distributed variables, the bias-corrected and accelerated (BCa) bootstrap method will be used to produce unbiased estimates of the confidence limits for all data (62). Data will be presented as mean and 95% confidence intervals of the bootstrapping procedure. The level of statistical significance will be *p* ≤ 0.05 for two-tailed tests. Magnitude of effects will be reported as Hedges' *g*, which is a corrected effect size based on Cohen's *d* that is suitable for use in small sample sizes of 20 or less per group to produce an unbiased estimate of the population effect size (63). The magnitude of the effect sizes will be considered to be small if they are ≥ 0.2, moderate if ≥ 0.6, and large if ≥ 1.2, using the scale proposed by Hopkins et al. (64). Adherence to the intervention will be assessed using the Wilcoxon signed rank test to compare baseline and follow-up classifications. The standardized test statistic of the Wilcoxon test will be converted to an effect statistic by dividing it by the square root of N (65), which can then be interpreted as *r* using the scales of Cohen (66) and Hopkins et al. (64).

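### Effects are labelled small, moderate or large from the point estimate of Hedges' g with no interval for g, although its standard error (about 0.33) exceeds the 0.2 cut-off for a small effect

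*Protocol article*

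**What the plan says.** Under Statistical Analysis, the protocol article chooses Hedges' g, "which is a corrected effect size based on Cohen's" d, because of the small groups. It then fixes the wording rule: the "magnitude of the effect sizes will be considered to be small if they are ≥ 0.2, moderate if ≥ 0.6". Large starts at 1.2. Nothing else enters the rule.

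The same section plans linear mixed models with office as a random effect and the baseline value as a covariate, a Sidak adjustment, and two-sided tests at 0.05. The 95% confidence intervals it mentions accompany means. None is stated for g. It does not say which SD standardises g, or whether the numerator is a raw or a model-adjusted difference.

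Under Sample Size the plan is to "recruit a total of 44 participants in two groups of 18 allowing for an attrition rate of 20" per cent. On the purpose of pilot studies, the section says: "their main purpose is to obtain an estimate of the standard deviation that could be used to determine the likely effect size to inform a" (the sentence ends by naming the later trial). Under Randomization: "The number of clusters is projected to be approximately eight with an average cluster size of six".

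**The concern.** A magnitude word taken from a point estimate is informative only if the estimate is precise relative to the width of the categories. Here the first cut-off is 0.2, and the sampling error of g at the planned size is clearly larger. The small-sample correction in Hedges' g removes bias but does not reduce noise. The word *small* could then be attached almost as readily to an outcome with no effect as to one with a small effect.

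Effect size is one of the things this pilot is meant to inform. Many outcomes are listed (activity, productivity, cardiometabolic and wellbeing measures), and each could carry a magnitude word. A reader could meet *small effect* beside a non-significant test, and the plan gives no way to reconcile the two.

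**Working it through.** **Inputs from the protocol article.** 18 completers per arm (Sample Size); about eight offices (Randomization); cut-offs 0.2, 0.6 and 1.2 (Statistical Analysis).

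**Assumptions, not in the document.** Four offices per arm, so 18/4 = 4.5 completers per office; intracluster correlation (ICC) 0 to 0.20; baseline to follow-up correlation r 0.5 to 0.9; true effect zero.

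**The plan's own figure.** 18 × 1.2 = 21.6, rounded up to 22 per arm, gives 44 in total. Dividing instead, 36/(1 − 0.2) = 45. The stated 44 is reproduced closely enough, and 18 per arm is the right basis for what follows.

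**Plain g, no clustering.**
- SE of g ≈ sqrt(2/18) = 0.333.
- Degrees of freedom = 34; correction J = 1 − 3/(4 × 34 − 1) = 0.978.
- P(|g| ≥ c) = 2 × P(t34 > (c/J)/0.333).
- c = 0.2: the t value is 0.614, probability 54.4% (27.2% in each direction).
- c = 0.6: the t value is 1.84, probability 7.4%.
- c = 1.2: probability 0.08%.

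So 54.4 − 7.4 = 47.0 percentage points of the false labels are *small*.

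**Plain g with office clustering.** Multiply the variance by 1 + (4.5 − 1) × ICC.

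| ICC | Design effect | SE of g | P(\|g\| ≥ 0.2), simulated | P(\|g\| ≥ 0.6), simulated |
|---|---|---|---|---|
| 0.05 | 1.175 | 0.361 | 58% | 10% |
| 0.10 | 1.35 | 0.387 | 60% | 13% |
| 0.20 | 1.70 | 0.435 | 65% | 18% |

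The simulations used 40,000 runs per setting, with offices of 5, 4, 5 and 4 completers in each arm.

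**Baseline-adjusted difference divided by the raw SD.** The variance is also multiplied by (1 − r²). Simulated P(|g| ≥ 0.2):

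| r | ICC 0 | ICC 0.10 |
|---|---|---|
| 0.5 | 49% | 56% |
| 0.7 | 41% | 48% |
| 0.8 | 32% | 40% |
| 0.9 | 18% | 24% |

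**Baseline-adjusted difference divided by the residual SD.** 54% to 66% over ICC 0 to 0.20, so baseline adjustment brings no relief with this standardiser.

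**What an interval would show.** Without clustering or baseline adjustment, the 95% half-width near zero is 1.96 × 0.333 = 0.65. An observed g of 0.20 would have limits of about 0.20 − 0.65 = −0.45 and 0.20 + 0.65 = 0.85. That runs from small in one direction to moderate in the other, which the single word *small* conceals.

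**The case against.** The strongest reply is that the label describes magnitude and is not the plan's test of an effect. Efficacy is judged by mixed models that include the office effect, with p values, and intervals are given for the means. Fixed published cut-offs are a common reporting convention. This stands: nothing in the section lets a label override a non-significant test. It does not remove the problem, because the magnitude statement itself carries no uncertainty.

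Three stronger readings are tempting, and the document does not support them.

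- A reader might infer that half of all outcomes would be mislabelled. The document does not fix this. The standardiser and the numerator of g are unstated and may be settled in a fuller plan. For outcomes that track strongly over eight weeks (body mass or waist might be examples, an assumption), the rate could be 18% to 40% with the raw SD.
- A reader might infer that chance labels would set the design of the full trial. The Sample Size section names the standard deviation as the quantity to be estimated. No section says that the labels will be used for planning.
- A reader might conclude that a label should be given only when the interval excludes zero. Without clustering or baseline adjustment, |g| would then have to reach about 2.03 × 0.333 × 0.978 = 0.66. *Small* could hardly ever be used, and only the largest estimates would be named. That turns a magnitude scale into a significance filter and favours exaggerated estimates.

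**Conclusion.** The point holds as a reporting weakness. The magnitude words rest on the point estimate of g, whose standard error of about 0.33 is larger than the first cut-off. Under no true effect, at least *small* would be assigned about 54% of the time for a plain g, and 58% to 65% at ICC 0.05 to 0.20. For a baseline-adjusted difference over the raw SD it would be 18% to 56% (r 0.5 to 0.9, ICC 0 to 0.10).

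False labels fall equally in both directions and are mostly *small*. For a plain g, *moderate* or above arises in about 7% without clustering and about 18% at ICC 0.20. Only the 18 per arm, the approximate number of offices and the cut-offs come from the document. The equal split of offices, ICC and r are assumptions. The sample size and the primary test of workplace sitting are unaffected.

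**What to change.** In the Statistical Analysis section:

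1. Report every g with a 95% confidence interval derived from the mixed model, so that it carries the office effect.
2. Name the SD used as standardiser, and say that the numerator is the model-adjusted difference if that is intended.
3. Keep the existing cut-offs, but describe magnitude by the range of categories that the interval covers. Call the effect unclear when the interval spans effects in both directions. Do not make the label conditional on significance.

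The cost is one extra column in the results tables and less definite magnitude wording. No change to the design, the sample size or the data collected is needed.

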## Discussion

This pilot cluster-randomized controlled trial will evaluate the efficacy of a tailored workplace intervention for reducing and breaking up sitting, productivity, wellbeing and cardiometabolic risk biomarkers. The multi-component intervention protocol was designed using a participatory approach informed by the BCW and identification of intervention functions, policy categories and BCTs using the APEASE criteria to enhance the intervention's adherence and effectiveness. In addition to employing this systematic and evidence-based process for developing the intervention, further strengths of this study include the cluster-randomized design to minimize contamination between groups that are located within the same organization. The study will also be conducted within an ecologically valid office environment, thus enhancing its real-world application. Ecological momentary assessment will be used to assess temporal effects of the intervention on productivity during specific postures and work activities; this may provide important evidence to encourage changes in workplace policy and practice. Potential limitations include sample representativeness of the general office worker population as the study is being conducted only within two organizations. It will also not be possible to determine the effects of each individual strategy used as part of the intervention, which could help in determining their suitability for inclusion in occupational health promotion programmes. Furthermore, physical activity levels prior to taking blood samples will not be standardized. This may be a limitation as there is the potential for carryover effects of prior exercise on glucose and lipid levels.

In conclusion, this study will provide important evidence regarding the efficacy of a systematically developed tailored workplace intervention. This will include evaluating the effects of the intervention on a range of health and work-related outcomes, including an ecological momentary assessment of productivity that has been seldom employed in office workplace studies; this may be key in promoting the adoption and implementation of such interventions in workplace practice and policies. The findings of this study can be used to inform a future fully powered RCT to determine the effectiveness of this multi-component intervention for reducing sitting and improving health in office workers.

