4.1 Instruction on how to perform the behavior	Advise or agree on how to perform the behavior (includes “Skills training”) Note: when the person attends classes	Psychological capability	Skills; Knowledge	Training; Education	Guidelines	A face-to-face training session will be provided to the participants by one member of the research team on how to break up sitting using prompt software and a height-adjustable workstation. Definition of prolonged sitting (sitting > 30 min) will be provided and participants will be advised to not sit more than 30 min in one continuous bout (28, 38). Participants will be provided with a leaflet containing information on the recommended sitting time guidelines, which states that office workers should be on their feet at work, for a minimum of 2 h initially and progressively increase to 4 h per day.
5.1 Information about health consequences	Provide information (e.g., written, verbal, visual) about health consequences of performing the behavior	Psychological capability; Reflective motivation	Knowledge; Belief about consequences	Education; Persuasion	Communication/Marketing; Guidelines	A face-to-face information session will be organized, and participants will be educated about information regarding the health consequences of prolonged sitting and the benefits of breaking up sitting. A leaflet containing the information will also be provided.
5.6 Information about emotional consequences	Provide information (e.g., written, verbal, visual) about emotional consequences of performing the behavior	Psychological capability; Reflective motivation	Knowledge; Belief about consequences	Education; Persuasion	Communication/Marketing	Verbal information regarding some of the emotional consequences (such as anxiety and depression) of prolonged sitting will be provided during a 10-min information session.
6.1 Demonstration of the behavior	Provide an observable sample of the performance of the behavior, directly in person or indirectly	Psychological capability	Skills; Knowledge	Training; Education; Modeling; Persuasion	Guidelines, Communication/Marketing	A step-by-step guide on how the intervention is being delivered will be provided to participants in a leaflet and a demonstration of intervention components will be delivered to participants (27).

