7.1 Prompts/cues	Introduce or define environmental or social stimulus with the purpose of prompting or cueing the behavior.	Physical opportunity; Psychological capability	Environmental context and resources; Memory, attention and decision processes	Environmental restructuring; Enablement	Environmental/Social planning	Prompt software will be installed on participants' computers. This software will be used to provide reminders to change between sitting and standing, and to remind participants to take short breaks (e.g., walking) based on participant preference.
8.1 Behavioral practice/rehearsal	Prompt practice or rehearsal of the performance of the behavior one or more times in a context or at a time when the performance may not be necessary, in order to increase habit and skill	Physical opportunity	Environmental context and resources; Skills	Environmental restructuring; Training	Environmental/Social planning	A Work-Fit-T Sit-Stand Desktop Workstation (Ergotron, St Paul, MN, USA) will be installed at participants' regular desks. This will provide them with the opportunity to alternate between sitting and standing while working.
8.2 Behavior substitution	Prompt substitution of the unwanted behavior with a wanted or neutral behavior	Physical opportunity; Psychological capability	Environmental context and resources; Memory, attention and decision processes	Environmental restructuring; Enablement	Environmental/Social planning	Installation of a Work-Fit-T Sit-Stand Desktop Workstation (Ergotron, St Paul, MN, USA) and prompt software on participant's computers will be used to provide reminders for participants to alternate between standing and sitting and form new habits around sitting less. Participants will be encouraged within the information leaflet and meeting with a researcher to intermittently substitute sitting with standing work
8.3 Habit formation	Prompt rehearsal and repetition of the behavior in the same context repeatedly so that the context elicits the behavior					
8.4 Habit reversal	Prompt rehearsal and repetition of an alternative behavior to replace an unwanted habitual behavior					

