#### Primary Outcome Measure: Workplace Sitting Time

The primary outcome measure is sitting time at work, which will be measured using an activPAL3 activity monitor (PAL Technologies Ltd., Glasgow, UK). The activPAL is a portable lightweight device, which is usually worn on the front of the mid-thigh to take measurement of postural information by recognizing periods of lying down/sitting, standing, and stepping based on the inclination of the thigh (39, 40). The activPAL has high reliability and validity for assessing sitting, standing and stepping (41). In this study, the device will be worn on the right thigh for seven full consecutive days (42) at baseline and during the last week of the intervention. The device will be waterproofed by wrapping it within a nitrile sleeve and an adhesive medical dressing. In addition, participants will complete a diary to keep record of their waking time, working hours and time they go to bed while wearing the device to enable calculation of waking and working time wear periods (42). Data from the activPAL will be considered valid only if the device is worn for a minimum of 75% of the workplace monitoring time (39, 40). The sitting time at work variable will be normalized by expressing it as a percentage of the duration of the working day for each participant.

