##### Productivity

Work productivity will be assessed using measures of absenteeism, presenteeism, and ecological momentary assessment (EMA) at baseline and during week eight of the study. Absenteeism will be measured using self-report at baseline and at the end of the eighth week. Three questions to assess unsanctioned absences will be used from a previous study (45). This includes the number of days off work in the last 2 weeks for sickness (colds, flu, etc.), the number of days off work for mental health reasons (stress, burnout, etc.), and the number of days excused work (e.g., compassionate leave, educational leave, parental leave). Self-reported absenteeism will be calculated by summing the number of days reported across all three questions. Presenteeism will be measured using the 8-item Work Limitations Questionnaire (WLQ), which is a short version of the original 25-item WLQ (46). This version of the WLQ is a reliable and valid alternative to the longer questionnaire (47). The WLQ requires participants to self-report their level of difficulty (or ability) to perform eight specific job demands in the last 2 weeks, with answers grouped into four work limitation scales on time management, physical, mental, and output demands.

The final measure of productivity is EMA, which has been used previously in a variety of different contexts to measure physical activity and sedentary behavior (48–50). Prompt software will be installed on participant's smartphones to deliver the EMA. Prompts to complete the EMA will occur at random, four times each week day between 9 am to 5 pm (51). In total, participants will be requested to respond to and complete a maximum of 12 EMA surveys in a week. Once a participant has completed 12 surveys, the prompt software will no longer prompt that participant to respond (51). The questionnaire includes items about posture, musculoskeletal issues, task being performed, social interactions, mood, and perception of engagement and productivity (Table 5), typically taking <1 min to complete each time.

**Table 5 T5:** Ecological momentary assessment productivity questions.

**Survey question**	**Responses**
What posture are you in?	Sitting/Standing/Walking
Are you experiencing musculoskeletal pain right now?	Yes/No
What are you currently doing?	In a meeting/Working at my desk/Working away from my desk/Eating/In transit/On a break/Other

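### The Discussion promises an intervention effect on EMA productivity within postures and activities, but posture is reported after randomisation and is what the intervention changes, so no such effect is a randomised comparison

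*Protocol article*

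**What the plan says.** In the Discussion of the protocol article the aim is causal and conditional: "Ecological momentary assessment will be used to assess temporal effects of the intervention on productivity during specific postures and work activities". The same sentence says this may help to encourage changes in workplace policy and practice.

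Statistical Analysis gives two models that bear on it:

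- A general model: "Linear mixed models will be used with arm and time as fixed effects", with the baseline value of each variable as a covariate. It does not contain posture.
- A posture model, whose purpose is stated first: "An additional linear mixed model will be used to compare the effect of standing vs. sitting posture for the EMA variables at follow-up". Its terms are then listed, and arm stands next to posture among them: "with posture and arm as fixed effects, participant ID and cluster ID as random effects". The baseline value is again a covariate. No arm-by-posture term is named, and no model contains work activity.

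Posture comes from the EMA questionnaire (Table 5, under Productivity), which asks "What posture are you in" at each prompt.

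The intervention acts on that same variable. Of the sit-stand workstation, Table 4 says: "This will provide them with the opportunity to alternate between sitting and standing while working". The leaflet asks workers to be on their feet "for a minimum of 2 h initially and progressively increase to 4 h per day". Under the primary outcome heading: "The primary outcome measure is sitting time at work". The Control Group section leaves controls' routine and environment unchanged.

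**The concern.** At follow-up, the posture reported at a prompt is a consequence of allocation. Comparing arms among seated prompts, among standing prompts, or with posture held fixed in a model has two consequences.

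1. **It removes the path through standing.** If standing raises or lowers productivity, that part of the intervention's effect is taken out of the arm coefficient.
2. **It compares selected moments.** Task, energy or pain at the time may influence both posture and the rating. Because the arms reach a given posture under different conditions, those moments are no longer alike between arms, even if the workers are.

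Work activity has the same difficulty in part. The prompt software encourages short breaks such as walking, and the activity item in Table 5 includes being on a break and working away from the desk.

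At stake is the productivity result. The Introduction says managers may be reluctant to adopt such interventions if productivity suffers. A within-posture arm difference read as randomised evidence could differ from the true intervention effect in size or sign. The limitations in the Discussion do not say that such comparisons are observational.

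**Working it through.** The plan gives no figure on this point, so there is none to reproduce. The check has two parts: whether the texts match, and how far a posture-adjusted arm coefficient can move.

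**Texts side by side**

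| Place | Question posed |
|---|---|
| Introduction | how posture and activities affect work performance over the day |
| Statistical Analysis, additional model | standing versus sitting at follow-up, with arm also in the model |
| Discussion | effects *of the intervention* during specific postures and activities |

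The first two agree; the third asks something else. The only model with posture has main effects alone, so it gives one common arm coefficient at fixed posture, not one per posture. Adding an arm-by-posture term would give separate contrasts with the same selection problem.

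**Relation between the two arm coefficients**

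For a linear model with balanced data and the same weights in both fits:

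adjusted arm coefficient = total arm effect - (posture coefficient x arm difference in share of standing prompts)

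The two agree only if the arms do not differ in standing or the fitted posture coefficient is zero.

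**Inputs from the document**

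- Control: the Introduction cites 79% of the working day spent sitting, so 21% not sitting. This is an upper limit for standing, since it includes stepping.
- Intervention: 2 h rising to 4 h on the feet. With an assumed 8 h day, 2/8 = 25% and 4/8 = 50%, with 37.5% as the midpoint.
- At most 12 surveys per week; ratings from 1 to 10.

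**Case A: the effect acts only through standing** (assumed benefit 0.5 points, no common cause)

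| Intervention share | Total effect | Adjusted arm coefficient |
|---|---|---|
| 25% | 0.5 x (0.25 - 0.21) = 0.020 | 0 |
| 37.5% | 0.5 x (0.375 - 0.21) = 0.0825 | 0 |
| 50% | 0.5 x (0.50 - 0.21) = 0.145 | 0 |

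**Case B: neither arm nor posture has any effect, but an unmeasured momentary state influences both posture and rating**

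This was simulated with 40,000 people, 12 surveys each, and a random intercept per person, without clusters or a baseline covariate. The assumed strengths are, per SD of the state, a log-odds slope for standing and a change in rating points: 0.5 and 0.5 (mild), or 1 and 1 (strong). The standing shares below are those realised in the simulation.

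| Target share | Strength | Posture coefficient x difference in standing | Simulated: adjusted minus unadjusted arm coefficient |
|---|---|---|---|
| 25% | mild | 0.244 x (0.26 - 0.22) = 0.010 | -0.002 - 0.008 = -0.010 |
| 25% | strong | 0.839 x (0.28 - 0.25) = 0.025 | -0.029 - 0.000 = -0.029 |
| 37.5% | mild | 0.234 x (0.38 - 0.22) = 0.037 | -0.028 - 0.010 = -0.038 |
| 37.5% | strong | 0.849 x (0.40 - 0.25) = 0.127 | -0.123 - 0.002 = -0.125 |
| 50% | mild | 0.231 x (0.50 - 0.22) = 0.065 | -0.058 - 0.006 = -0.064 |
| 50% | strong | 0.831 x (0.50 - 0.25) = 0.208 | -0.202 - 0.009 = -0.211 |

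The shift is therefore about -0.01 to -0.21 points where the truth is zero. If the common cause is a stable trait of the person instead, the shift reaches only about -0.02 (at 50% and the strong setting, -0.048 - (-0.028) = -0.020). The model without posture recovered the total effect, within simulation error, in every setting.

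**Scale of sampling error**

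Assume rating SDs of 1.2 between and 1.5 within persons and 10 answered prompts. The SD of a person's mean is sqrt(1.2² + 1.5²/10) = 1.29. With 18 per arm the standard error of an arm difference is 1.29 x sqrt(2/18) = 0.43 points, before any allowance for clustering.

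**The case against.** The strongest reply is that the plan never commits the error. Statistical Analysis gives the posture model a different job, standing versus sitting, and arm can be read there as an adjustment term. The general arm-and-time model has no posture in it and, as worded, covers each variable, including the EMA items. The Introduction describes the EMA purpose in the same way. What remains is one loosely worded, hedged sentence in the Discussion about a secondary outcome of a pilot. The illustrative shifts are also smaller than the standard error of about 0.43 points.

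Most of this stands, and it rules out several stronger readings that a reader might infer:

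- *That the posture model's arm coefficient will be reported as the intervention effect.* The article nowhere says so.
- *That the randomised EMA comparison is lost.* It appears to be available from the arm-and-time model.
- *That seated controls had no choice but to sit.* The article does not say this. Table 5 allows walking, meetings, breaks and work away from the desk in either arm.
- *That the bias is known to be sizeable.* Assuming 5% standing in control against 35% in intervention, with other assumed confounding strengths, gives -0.08 to -0.27 points. The 5% is not in the article, whose only related figure is about 21% not sitting.

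The reply does not remove the Discussion sentence. It asks for an effect of the intervention within postures and activities, and no analysis of this design delivers that as a randomised comparison. A small expected bias does not change what the quantity means, and large sampling error is no protection against reading it causally.

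**Conclusion.** The point holds as a fault in the stated aim and its interpretation, not in the main analysis. The Discussion promises a causal conclusion within postures and activities that the design cannot support, because posture, and partly activity, follows allocation and is what the intervention changes. Any arm effect within or adjusted for posture is not a randomised comparison and excludes what acts through standing. That conclusion is structural and needs no particular numbers.

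The size is unknown. Illustratively, the shift is about 0 to -0.2 points on the 1-10 scale when there is no true effect, depending on the assumed confounding and shift in standing. If the effect acts only through standing, all of it is lost (0.145 points at most in the cases worked). These figures rest on an 8 h day, the 79% sitting figure standing in for controls, an assumed 0.5-point benefit, and assumed confounding strengths. Since the outcome is secondary and the trial a pilot, this limits what can be concluded about productivity. It does not threaten the primary result.

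**What to change.** In Statistical Analysis:

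- State that the intervention effect on each EMA item is taken from the model without posture or activity.
- State that arm enters the posture model as an adjustment term only, and that neither its coefficient nor any posture- or activity-specific arm contrast will be reported as an intervention effect.
- Describe the standing-versus-sitting result as an observational association and not as an effect.

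In the Discussion, reword the EMA sentence to match: EMA gives the overall intervention effect on momentary ratings and, separately, a descriptive association between posture and ratings. Add to the limitations that posture at a prompt is measured after randomisation.

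The cost is wording only, with no change to data collection or sample size. The trial gives up a causal within-posture claim that it could not have supported.
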